#### **10.3.3 Deviation(s) from the original statistical plan**

Any deviation from the planned analyses will be listed and justified in the study report.

### **10.4 Handling of missing data and drop-outs**

Any missing data or drop-outs from will be listed and justified in the study report.

## **11. QUALITY ASSURANCE AND CONTROL**

### **11.1 Data handling and record keeping / archiving**

#### **11.1.1 Case Report Forms**

Demographic data (age, BMI, sex, type of surgery) will be obtained from the departmental electronic anaesthesia information system AIS. Consent forms will be obtained at the pre-anaesthesia visit. All study data will be directly recorded in the CRF, which should also be considered being source data. These data will be transferred into the departmental research documentation system – LabKey, as this is routine in our research practice (see below).

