| Measurements and procedures: | 
Eligible, consenting adults will be prepared for general anaesthesia in the usual way consisting of EKG, pulse-oximetry, Narcotrend™, a venous cannula and an arterial line for continuous blood pressure monitoring. They will receive additional non-invasive monitoring for this study, such as transcutaneous measurement of pCO2 and O2, NIRS, and thoracic electrical impedance tomography (EIT, PulmoVista® 500, Draeger, Luebeck, Germany)
 
Standard pre-oxygenation (until etO2 is > 90% or time > 3 minutes) will be done. Anaesthesia will be started (= "induction") using Propofol and Fentanyl i.v., using Narcotrend™ to measure depth of anaesthesia. All patients will receive a standard dose (Rocuronium, 0.9mg/kg) of neuromuscular blockage to facilitate airway management and total intravenous anaesthesia will be installed to maintain anaesthesia. Train of four measurement (TOF) will be confirmed full neuromuscular blockage with Rocuronium every 30 seconds. If necessary, additional dosage of neuromuscular blockage will be administered.
 
After administration of Rocuronium, possibility of mask ventilation will be confirmed and the sealed envelope with the randomization will then be opened. As a study intervention, the assigned method (HFNCT 70 l/min with either jaw thrust or laryngoscopy, or 10 l/min or 2l/min) will be installed and mask ventilation discontinued starting the apnoea period. Nasopharyngoscopy (EF-N slim, Acutronic, Hirzel, Switzerland) will confirm upper airway patency. Blood gas analysis will be conducted: baseline awake, start of apnoea, first minute after apnoea start, every 2 minutes thereafter with a maximum of 75ml in total. Other measurements (ECG, pulse-oximetry, blood pressure, NIRS, thoracic EIT, Narcotrend™, PtcO2, PtcCO2) will be measured continuously over the study period.
 
The study intervention will end when one of the following criteria (study end-points) is met: SpO2 <92%, PtcCO2 > 80 mmHg, pH < 7.10, potassium > 6.0 mmol/l, or time > 15 minutes.
 
When any of the end points is reached, patient-centred standard anaesthesia care will be continued, as planned for the case.
 
A post-operative interview will be conducted on the first post-operative day to evaluate injuries during airway management (e.g. bleeding, sore throat, hoarseness, lip injuries), pain, postoperative nausea and vomiting.
 |

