Eine der folgenden vier Massnahmen wird anschliessend durchgeführt: THRIVE mit 70 l/min unter Anwendung des Esmarch Manövers (jaw thrust), THRIVE mit 70 l/min unter permanenter Laryngoskopie (Kontroll-Gruppe), 10 l/min mit Esmarch oder 2 l/min mit Esmarch.

Währenddessen werden EKG, Pulsoxymetrie, Narcotrend™, transkutanes pCO2 und pO2, NIRS, Elektrische-Impedanz-Tomographie, Blutdruck und Herzzeitvolumen (mit FloTrac über Pulsdruckkurven) kontinuierlich aufgezeichnet. Ausserdem werden alle zwei Minuten arterielle Blutgasanalysen durchgeführt.

Die zugeteilte Massnahme erfolgt bis entweder SaO2 < 92%, PtcCO2 > 80 mmHg oder Zeit > 15 Minuten aufgetreten sind. Sollte der pH < 7.10 fallen oder das Kalium > 6.0 mmol/l steigen, wird das Experiment ebenfalls abgebrochen.

Anschliessend wird der Atemweg gesichert und normal mit der Anästhesie fortgefahren.

Bevor der Patient entlassen wird, führen wir eine Befragung durch, wo allfällige Nebenwirkungen und Komplikationen des Atemwegmanagements erfragt werden.

Unsere Hauptfrage ist, wie unterschiedliche Flussraten und Mundöffnung die CO2 Auswaschung beeinflussen, wobei wir davon ausgehen, dass die tieferen Flussraten nicht relevant schlechter sind. Zusätzlich werden wir mit NIRS nicht invasiver Messung über der Haut der Stirn den Effekt des erhöhten CO2 auf die zerebrale Durchblutung messen, mittels EIT bestimmen wir Änderungen der funktionellen Residualkapazität der Lungen und wir können über Veränderungen Aussagen über potentiell auftretende Atelektasen treffen. Ausserdem können auch arterielle Messungen von pO2 und pCO2 mit den transkutanen Messungen verglichen werden.

Durch die Erkenntnisse dieser Studie erwarten wir, in Zukunft die apnoeische Oxgenation auch mit niedrigeren Flussraten durchführen zu können, was nicht nur weniger O2 verbraucht, sondern auch materialtechnisch gesehen deutlich billiger ist. Auch ist die

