### **6.2.2 Blinding procedures**

Patients are under general anaesthesia therefore blinded to the treatment group, but due to the different oxygen delivery systems study personnel in the operating theatre cannot be blinded.

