### 8.5.2 Assessment of secondary outcomes

Time to desaturation below 92% will be measured using a stopwatch. If desaturation does not set in, the experiment will end once 15 minutes have been completed.

Arterial blood pressure will be measured using a catheter in the radial artery. ECG and pulse oximetry will also be measured. These measurements are normal anaesthesia care.

From the arterial catheter blood samples will be drawn for blood gas analyses.

Brain oxygenation as a surrogate of brain perfusion will be assessed by cerebral NIRS, using Niro-200NX (Hamamatsu, Tokyo, Japan) monitor continuously. This is also a standard procedure without complications, especially during cardiac surgery.

EIT will be continuously measured using PulmoVista® 500 by Dräger, Lübeck, Germany, to visualize possible atelectasis and its progression over time.

EIT is a non-invasive, radiation-free technique for the assessment of spatial and temporal ventilation distribution based on the changes in electrical properties of the tissue during the respiratory cycle. EIT measurements will be performed using a commercially available setup (PulmoVista 500, Draeger, Germany). A loose-fitting belt with 16 evenly spaced electrodes will be placed around the participant's chest in thoracic median plane. Small electrical currents are injected through adjacent electrodes in a rotating mode. Resulting potential differences are measured, and impedance distribution sampled at 30 Hz will be calculated by an automated linearised newton-raphson reconstruction algorithm [19]. Relative change in end-expiratory lung impedance (EELI) and measures of ventilation inhomogeneity such as the global inhomogeneity index (GI) will be calculated as described previously using customized software (Matlab R2013a, The MathWorks Inc., Natick, MA, USA) [20, 21].

After securing the airway, the highest etCO2 measured during the first minute will be recorded.

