#### **11.1.2 Record keeping / archiving**

All study data will be archived for a minimum of 10 years after study termination or premature termination of the clinical trial.

Data will be transferred into a secure, web-based data integration platform (LabKey, LabKey Software, Seattle, WA, USA, version 14.3) and controlled independently by two members of the study team. Additionally, data are double-checked by comparing the screening records with the digital anaesthesia documenting system of the hospital.

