### **11.2.4 Electronic and central data validation**

Data are being validated by the primary investigator and the sponsor when evaluating the results

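### The CRF is made the source for ptcCO2 that is already continuously recorded, with no planned check against that record and with validation tied to evaluation of the results

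*Protocol*

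**What the plan says.** **Source.** Section 11.1.1 takes demographic data from the anaesthesia information system. For the rest: "All study data will be directly recorded in the CRF, which should also be considered being source data".

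**Who knows the arm.** Section 6.2.2: "study personnel in the operating theatre cannot be blinded".

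**What is recorded anyway.** The synopsis lists ptcCO2 and pulse oximetry among signals that "will be measured continuously over the study period". The local-language summary goes further. Its list of signals, which includes transcutaneous pCO2 and pulse oximetry, ends "Blutdruck und Herzzeitvolumen (mit FloTrac über Pulsdruckkurven) kontinuierlich aufgezeichnet", that is, continuously recorded.

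**How the outcomes are obtained.** Under 8.5.1 the primary outcome is the difference in ptcCO2 divided by the measurement time, counted from when the rise has become linear, after a delay of about 60 to 90 seconds. Under 8.5.2: "Time to desaturation below 92% will be measured using a stopwatch".

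**Checks.**
- 11.1.2: data moved into LabKey are "controlled independently by two members of the study team".
- 11.1.2: "data are double-checked by comparing the screening records with the digital anaesthesia documenting system of the hospital".
- 11.2.2: LabKey logs each change of data.
- 11.2.4: "Data are being validated by the primary investigator and the sponsor when evaluating the results".
- 11.3: a nurse with no other part in the study controls all data weekly for validity and completeness. There is no external monitoring.

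**The concern.** The primary endpoint rests on the difference between CO2 readings and on a judgement of when the linear rise begins. The only source named for those readings is a form, in a study whose theatre staff know the allocation. An instrument record that does not depend on the observer is made for the same signal, but it is neither named as source nor used to verify the form.

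The timing of validation adds to this. If the investigator and sponsor validate while they evaluate results, queries and corrections may be raised with the arm results in view. Nothing in the protocol requires the data to be closed first.

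The direction matters because this is a non-inferiority trial, and 10.1 says the primary hypothesis was based on a pilot that found no differences by flow rate or mouth opening. A reading or correction that leans towards the expected result leans towards declaring success. Section 2.1.3 argues that the anaesthetist cannot influence apnoea time; it does not address how CO2 readings are recorded.

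**Working it through.** **1. Does any stated check compare CRF ptcCO2 with the trace?**

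| Check | Section | Object or reference named | CRF ptcCO2 against trace? |
|---|---|---|---|
| Two-person control | 11.1.2 | Data transferred to LabKey | Not stated |
| Comparison with the hospital anaesthesia record | 11.1.2 | Screening records | No |
| Audit log | 11.2.2 | Changes within LabKey | No: shows that a value changed, not whether it was right |
| Investigator and sponsor validation | 11.2.4 | None named | Not stated |
| Weekly nurse control | 11.3 | All data; no reference record named | Not stated |
| Serial arterial pCO2 | 6.1, 8.5.3.2 | A separate measurement; the local-language summary foresees comparing it with the transcutaneous values | Not stated as verification of the CRF |

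No row verifies the primary readings against the continuous record.

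**2. The plan's own sample size.** Section 10.2 gives margin 0.3 mmHg/min, SD 0.35 mmHg/min, one-sided alpha 0.025 and power 80%.

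n per group = 2 × (1.960 + 0.842)² × 0.35² / 0.3² = 21.4, rounded up to 22. This matches the protocol, which then includes 25 per group. No figure in the protocol is disputed here.

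**3. How sensitive the contrast is to reading bias.** The size of the bias is an assumption; the protocol gives none.

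- Window: 15 minutes less 90 s = 13.5 min; 15 minutes less 60 s = 14 min.
- A bias b (mmHg) in the mean end-minus-start difference between two arms shifts the contrast by b / window.
- b = 1: 1/13.5 = 0.074 and 1/14 = 0.071 mmHg/min. As a share of the margin: 0.074/0.3 = 25% and 0.071/0.3 = 24%.
- b = 0.5: 0.037 and 0.036 mmHg/min, about 12% of the margin.
- A bias equal to the whole margin would need 0.3 × 13.5 = 4.05 to 0.3 × 14 = 4.2 mmHg.

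**4. Effect on the one-sided error when the true loss equals the margin.** Standard error of a contrast = 0.35 × √(2/n): 0.0990 for n = 25 and 0.1055 for n = 22. If the bias favours the experimental arm, the chance of declaring non-inferiority is that of a t statistic with 2n − 2 degrees of freedom and non-centrality shift/SE exceeding its 2.5% critical value.

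| Assumed bias | n per arm | Shift/SE | One-sided error |
|---|---|---|---|
| 0 | either | 0 | 2.5% |
| 0.5 mmHg | 25 | 0.36 to 0.37 | 5.4 to 5.6% |
| 0.5 mmHg | 22 | 0.34 to 0.35 | 5.2 to 5.3% |
| 1 mmHg | 25 | 0.72 to 0.75 | 10.5 to 11.0% |
| 1 mmHg | 22 | 0.68 to 0.70 | 9.7 to 10.1% |

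A normal approximation gives nearly the same for 1 mmHg: 10.8 to 11.3% at n = 25 and 10.0 to 10.4% at n = 22.

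**The case against.** The strongest reply is that the data trail is better than the two sentences in 11.1.1 and 11.2.4 suggest.

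- Arterial blood gases are drawn at the start of apnoea, at one minute and every two minutes after that, giving an analyser pCO2 series over the same period. The highest end-tidal CO2 in the first minute after the airway is secured is a further value. A shift in one arm's transcutaneous readings could be looked for against these.
- LabKey logs every change, so a late correction there leaves a trace.
- An uninvolved nurse controls all data weekly, and nothing limits what that nurse may consult.
- Section 11.1.1 cannot be wholly literal: 8.5.2 processes impedance data sampled at 30 Hz in dedicated software.
- Lock timing and query handling are often set out in a data-management plan or SAP, which is not to hand.

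Much of this stands, and it rules out three stronger readings that a reader might infer. First, that the values are hand entries: the protocol says only that data go directly into the CRF, and it does not say how or by whom. Second, that the ptcCO2 values cannot be checked: nothing says the trace is discarded, and 11.1.2 archives all study data for at least 10 years. Third, that nothing exists against which an error could be detected: the arterial series, the audit log and the nurse control contradict that.

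What the reply does not remove is that the protocol names the CRF as source and fixes when the investigator and sponsor validate. Those are its own statements, not gaps left for another document, and none of the protections is stated to verify the CRF ptcCO2 values used for the primary slope.

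**Conclusion.** The point holds as one about source and sequence. The protocol makes the CRF the source for a primary signal that it also records continuously, plans no check of one against the other, and ties investigator and sponsor validation to the evaluation of results. That wording permits corrections after results by arm are seen; it does not say that this will happen.

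The partial protections lower the risk without closing it. The 10 to 11% error shows sensitivity only. It rests on an assumed 1 mmHg bias that is systematic, runs in one direction, does not cancel between start and end readings, and acts over the full window of 13.5 to 14 minutes. No part of the protocol supports that size or direction, and a bias against the experimental arm would cost power instead. The sample size is unaffected. The change is worth making because the better source already exists and the cost is small.

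**What to change.** **Section 11.1.1.** Name the time-stamped monitor export as the source for ptcCO2, SpO2 and the other continuously recorded signals. Keep the CRF as source for events and items observed manually. State that the primary slope and the time to SpO2 below 92% are derived from the export by one scripted rule, including a fixed rule for where the linear phase begins, applied identically to all four arms. The stopwatch time in 8.5.2 can stay as a cross-check.

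**Section 11.2.4.** Require validation and database lock before any outcome is tabulated by arm. The weekly nurse control in 11.3 can carry the comparison of CRF values with the export.

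**Cost.** One export per patient, a few sentences of protocol text and slightly more data handling. There is no change to sample size, staffing or patient procedures.

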#### **11.1.2 Record keeping / archiving**

All study data will be archived for a minimum of 10 years after study termination or premature termination of the clinical trial.

Data will be transferred into a secure, web-based data integration platform (LabKey, LabKey Software, Seattle, WA, USA, version 14.3) and controlled independently by two members of the study team. Additionally, data are double-checked by comparing the screening records with the digital anaesthesia documenting system of the hospital.

## **11.2 Data management**

### **11.2.1 Data Management System**

At the research platform darwin (darwin.insel.ch) there are three locally separated dedicated servers installed for research data management. Host names are darwin0015 (productive instance), darwin0016 (backup instance) and darwin0017 (test instance). The servers are running on Windows Server and using SQL Server (Microsoft Corporation, [name]) for the relational database.

In order to comply with the federal act on research involving human being (HRA) LabKey Server [22] of LabKey Organisation (LabKey Corporation, [name]) is the dedicated software application. The web application LabKey Server is implemented in Java and is running on the Apache Tomcat web server. The data are stored in relational database engines like PostgreSQL or Microsoft SQL server [22].

### **11.2.2 Data security, access and back-up**

LabKey Server provides web application security. LabKey Server can be configured for Secure Socket Layer (SSL) encrypted data transfer if needed.

The application has a group and role-based security model. Each user belongs to one or more security groups with specific sets of permissions in relation to folder or projects in the system. Only dedicated site administrators have access to the admin console enabling user management and changing security settings.

Data are stored and visualized in data grids either in the format of datasets, lists or assays. Each change of data is tracked and documented in corresponding audit log files.

The system can only be accessed entering a user name and password. All events are recorded in the user event list of the audit log files.

The application is running on a productive server with an image on a backup server. In addition, a regularly backup of the whole database is implemented using storage servers (darwinnas0001 and darwinnas0002) hosted at the darwin.insel.ch domain.

### **11.2.3 Analysis and archiving**

LabKey Server provides data analysis by integrated tools for creating filtered views and charts.

All data can be exported in different formats (excel, text, queries) suitable for transfer to a statistical software package of choice. In addition, data can be analysed creating R views.

All data will be archived and secured in the database as long as required by legislation.

### **11.2.4 Electronic and central data validation**

Data are being validated by the primary investigator and the sponsor when evaluating the results

## **11.3 Monitoring**

A study nurse who is not involved in the study otherwise, will control all data for its validity and completeness on a weekly basis. External monitoring will not occur, as this is an investigator-initiated study with no external funding.

## 12. PUBLICATION AND DISSEMINATION POLICY

The results will be published in a peer-reviewed journal. Final decision on publishing the results will be kept by the project leaders. Authors of the publication will be team members who contributed to the design, conduct or analysis of the study and who approved of the final version of the manuscript.

## 13. FUNDING

### 13.1 Funding

This study is solely financed by a departmental research grant from the departmental anaesthesia research fund. There is no funding or financial influence through any other company. We will ask for sponsoring or reduced prices of FlowTrac sensors (Edward's LifeScience) and of OptiFlow nasal cannulas (Fisher&Paykel).

## 14. INSURANCE

Insurance will be provided by the Inselspital through Zürich-Versicherungs-Gesellschaft AG.  
Contract number: 15.369.591

